##### Mediation analyses

To examine the possible underlying mechanisms of change in MBSR, mediation analyses will be conducted. Only the data of the treatment-adherent sample will be included in these analyses. By means of a multiple mediation model suggested by Preacher and Hayes [75], we will test the mediating effect of mindfulness skills, self-compassion, rumination and adherence to MBSR on psychological distress, quality of life (only in patients), caregiver appraisal (only in partners), relationship quality and spirituality.

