##### Adherence to MBSR

is assessed during the entire study period with a calendar on which participants in the MBSR condition fill out on a daily basis whether they adhere to the mindfulness exercises: either formal practice (e.g. meditation exercise like the bodyscan), informal practice (e.g. activity with awareness) or no exercise. Adherence to MBSR has been shown to mediate the effects of MBCT on depressive symptoms [72].

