### Statistical analysis plan

#### Sample size

To determine the required sample size, first the sample size was calculated that would be needed for a simple *t*-test and subsequently it was corrected for clustering, repeated measurements and baseline. A two-sided *t*-test on the total HADS score [39,40] (i.e. our primary outcome measure, examining psychological distress (HADS-total), anxiety symptoms (HADS-A) and depressive symptoms (HADS-D)) would require 64 participants in each group to have 80% power to detect a medium-sized difference (effect size = 0.5) with alpha = 0.05. To correct for clustering, we multiplied this sample size of 64 with the design factor (1 + (*n* − 1) * ICC), where *n* denotes the cluster size and where ICC denotes the intra-cluster correlation. In our study, the treatment groups will consist of 14 people, of whom about 7 will be patients. With *n* = 7 and an estimated ICC = 0.01. [72], the correction factor equals 1.06. To correct for repeated measurements and the use of the baseline measurement as a covariate, we multiplied the required sample size by the design factor $\left(\left(1+\rho \right)/2-\rho_{0}^{2}\right),$ where *ρ* denotes the correlation between the post-treatment HADS measurements, and *ρ*_0_ denotes the correlation between the baseline HADS with the post-treatment HADS measurements. With *ρ* = 0.8 and *ρ* = 0.5 as conservative estimates, the second design factor equals 0.65. Consequently, after correction for clustering and covariates, we arrived at a required sample size of 0.65 * 1.06 * 64 = 44 patients per arm. So 88 patients with lung cancer would be required for the study. Based on our pilot study [[name], [name], [name], [name] and [name], in preparation], we expect a 20% drop-out rate. Therefore, we intend to include 110 patients and 110 partners.

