#### Primary analyses

The samples of lung cancer patients and partners will be analyzed separately. Baseline characteristics of the population will be compared between MBSR and control group to ensure that key variables were evenly distributed by randomization. First, analyses will be based on the intention-to-treat approach. Next, we will perform per-protocol analyses with the treatment-adherent sample (i.e. in the MBSR condition participants have to attend at least four of the eight MBSR sessions [73] and in the TAU condition participants do not attend a mindfulness-based programme).

We will use linear mixed models to analyze all outcome variables (i.e. psychological distress, quality of life (only for patient), caregiver appraisal (only for partner), relationship quality and spirituality), with treatment as fixed factor, baseline measurement as covariate and a random intercept based on MBSR group. This procedure will use all observed data in our analyses. In addition, Cohen’s *d* effect size [74] will be reported based on the difference between the group means on baseline and follow-up scores, divided by the pooled standard deviation at baseline and follow-up.

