## Discussion

In the last ten years MBSR has not only proven to be a feasible and acceptable intervention in cancer patients [76], but it also seems to be effective in reducing psychological distress [30]. However, the generalization of these results is limited because most participants were female patients with breast cancer. A large part of lung cancer patients already have advanced cancer at time of diagnosis and are confronted with a poor prognosis and low health status. Consequently, they more often report psychological distress than patients with other diagnoses of cancer [8,9]. Hence, it is not yet clear whether MBSR is a feasible, acceptable and effective intervention in patients with lung cancer. Moreover, little is known about the effectiveness of MBSR in partners of cancer patients [30], though they also often report psychological distress.

Our pilot study of 19 lung cancer patients and 16 partners participating in an MBSR course, provides preliminary evidence that MBSR is feasible and acceptable in this population ([name], [name], [name], [name] and [name], in preparation). The current trial will answer the question whether MBSR is effective in patients with lung cancer and their partners.

We started enrolment of participants in February 2012. At the moment, we think recruiting a sufficient number of patients and partners will be a challenge due to rapidly fluctuating health status and sudden changes in cancer treatment [77]. The main reasons for declining participation in patients is ‘being too ill’ or that it is ‘too much of a burden during chemo and/or radiotherapy’. Furthermore, no perceived need or motivation for the training is commonly mentioned. Among partners, participation is highly depending on whether the patient is willing to participate. Although partners can take part separately, partners who are interested do often not participate when the patients decline participation.

Considering the difficulty of studying lung cancer patients and their partners [77], our trial will offer valuable information on whether MBSR, as one of the few available psychosocial care programmes, contributes to the alleviation of their psychological distress.

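### Mediation is confined to an adherent sample defined by different post-randomisation rules in each arm, so the treatment-to-mediator path loses the protection of randomisation

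*Protocol article*

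**What the plan says.** The Mediation analyses section sets the analysis population in one sentence: "Only the data of the treatment-adherent sample will be included in these analyses". The population is defined under Primary analyses, separately for each arm. For MBSR, "in the MBSR condition participants have to attend at least four of the eight MBSR sessions". For TAU, "in the TAU condition participants do not attend a mindfulness-based programme".

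The same section opens the main comparison with the full randomised sample ("First, analyses will be based on the intention-to-treat approach") and puts the per-protocol analysis second. That order is not carried over to mediation, and the word *only* leaves no room for it.

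The mediators are listed as follows: "we will test the mediating effect of mindfulness skills, self-compassion, rumination and adherence to MBSR". They are tested against psychological distress, quality of life (patients), caregiver appraisal (partners), relationship quality and spirituality. The section Adherence to MBSR says that the last mediator is measured with "a calendar on which participants in the MBSR condition fill out on a daily basis".

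**The concern.** An indirect effect is the product of two paths: treatment to mediator (a) and mediator to outcome (b). The b path is observational in any trial. The a path is a comparison of randomised groups, and it keeps that standing only while the groups remain as randomised.

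Session attendance happens after allocation and can be observed only in the MBSR arm. The filter removes MBSR participants who attend few sessions but cannot identify or remove the TAU participants who would have done the same. The TAU rule is a different filter and probably removes few people. If those who attend differ from those who do not in health, distress or motivation, the retained arms differ on the mediator even where MBSR does nothing to it. The a path enters every indirect effect, so every mediator-outcome pair, in patients and in partners, is exposed.

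At stake is the conclusion about how MBSR works. The embedded process study could report a mechanism that is partly or wholly a selection effect, or miss a real one.

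**Working it through.** **The plan's own figures.** The document gives no number for the mediation analysis. Its sample size is needed only for the arm size, and it reproduces. A two-sided t-test with effect size 0.5, alpha 0.05 and 80% power needs 64 per group (exact power 0.801). Then 64 × 1.06 × 0.65 = 44.1, stated as 44 per arm; 2 × 44 = 88; and 88 / 0.80 = 110. With equal arms that is 110 / 2 = 55 per arm.

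**Inputs that are assumptions.** None of these is in the document.
- q, the share of MBSR participants attending fewer than four sessions: 10%, 20%, 30%.
- r, the correlation between attendance propensity and mediator: 0.3, 0.5. The positive sign is arbitrary; a negative r gives the same sizes with the sign reversed.
- b, the standardised mediator-to-outcome path: 0.5.
- The true effect of MBSR on the mediator: zero.
- The TAU filter removes nobody.

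**Formula.** If the lowest fraction q on a normally distributed propensity is removed from one arm, the mean mediator of those retained shifts by

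spurious a = r × φ(z_q) / (1 − q),

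where z_q is the q-quantile of the standard normal and φ its density. The spurious indirect effect is b × a.

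- q = 10%: φ / (1 − q) = 0.1755 / 0.9 = 0.195
- q = 20%: 0.2800 / 0.8 = 0.350
- q = 30%: 0.3477 / 0.7 = 0.497

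**Simulation check.** 55 per arm, 5,000 runs per setting. An indirect effect was declared when the a and b paths were both significant at two-sided 5%.

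| q | r | spurious a path (SD) | spurious indirect effect (0.5 × a) | simulated mean indirect effect | false-positive rate |
|---|---|---|---|---|---|
| about 0 | 0.3 / 0.5 | 0 | 0 | −0.002 / 0.000 | 4.9% / 5.2% |
| 10% | 0.3 | 0.058 | 0.029 | 0.028 | 5.9% |
| 10% | 0.5 | 0.097 | 0.049 | 0.052 | 8.4% |
| 20% | 0.3 | 0.105 | 0.052 | 0.050 | 7.6% |
| 20% | 0.5 | 0.175 | 0.087 | 0.085 | 13.9% |
| 30% | 0.3 | 0.149 | 0.075 | 0.074 | 10.0% |
| 30% | 0.5 | 0.248 | 0.124 | 0.126 | 21.6% |

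The first row is the analysis of all randomised participants. Simulation and formula agree. At r = 0.1 the spurious a path is only 0.02-0.05 SD, and at r = 0 it vanishes.

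**Limits.** The simulation has no clustering, no missing data and no baseline covariate. Adjusting for the baseline mediator would reduce the bias to the extent that attendance is predicted by it. The joint test stands in for the multiple mediation procedure that the plan names.

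**The case against.** **The analysis is secondary and exploratory.** This stands. It concerns possible mechanisms, and the main comparison, the secondary outcomes under intention to treat, the sample size and the cost-effectiveness analysis do not depend on it. It lowers the severity but does not remove the fault, because the restriction is written into the text and is not a detail left to another document.

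**The document does not show that attendance is related to prognosis.** This stands too. A reader might infer that the filter removes the sicker MBSR participants and so flatters MBSR, because the Discussion says recruitment will be hard "due to rapidly fluctuating health status and sudden changes in cancer treatment" and reports illness and treatment burden as main reasons for refusal. Those remarks concern declining to enrol, before randomisation, and not low attendance after allocation. The same paragraph also names lack of perceived need or motivation. If that reason drove low attendance, the filter could remove less distressed people and the bias could run the other way.

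**All-randomised mediation is not a complete cure.** Partly right. Some non-attenders may give no follow-up data, and the b path stays observational. Still, including those who are followed up drops a selection rule that the plan itself imposes.

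**The per-protocol comparison has the same filter.** True, but there intention to treat comes first and the per-protocol result is named as such, so the safeguard is present and no change is asked for.

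**Conclusion.** The point holds at moderate severity. Followed as written, the plan estimates every treatment-to-mediator path in arms selected by different post-randomisation rules, with no analysis of the randomised arms beside it. Under the assumed ranges (10-30% non-attendance, correlation 0.3-0.5, b = 0.5), this produces a spurious a path of about 0.06-0.25 SD, a spurious indirect effect of about 0.03-0.12 SD and a false-positive rate of about 6-22% against 5%. The bias is zero if attendance is unrelated to mediators and outcomes. Its actual size and direction cannot be derived from the document.

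Three stronger readings are not supported:
- TAU is not wholly unselected, since TAU participants who join a mindfulness-based programme are removed.
- The problem should not be sized by multiplying an assumed share removed by an assumed deficit and comparing it with the planned effect (for example 0.4 × 0.8 = 0.32 SD, and 0.32 / 0.5 = 64%). Both inputs are invented, and the 0.5 in "would require 64 participants in each group to have 80% power to detect a medium-sized difference (effect size = 0.5) with alpha = 0.05" belongs to the HADS comparison, not to an indirect effect.
- The trial's main conclusion is not in doubt.

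Adherence to MBSR as a mediator is a separate difficulty. The calendar exists only in the MBSR arm, and the sample has already been selected on attendance. There is no ordinary between-arm contrast for this variable in any analysis set.

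**What to change.** 1. For mindfulness skills, self-compassion and rumination, make mediation in all randomised participants, analysed as allocated, the main analysis.
2. Keep the treatment-adherent sample as a sensitivity analysis, labelled as a non-randomised comparison.
3. Take adherence to MBSR out of the list of mediators of the randomised contrast and report it as an association within the MBSR arm.

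A complier-average effect with four or more sessions as the exposure is not requested. It would assume that allocation does nothing for those attending one to three sessions, although they may still receive sessions, CDs and home practice.

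The cost is a change of wording, with no new data collection. The price in the results is that non-attenders somewhat dilute the indirect effects.

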## Discussion

In the last ten years MBSR has not only proven to be a feasible and acceptable intervention in cancer patients [76], but it also seems to be effective in reducing psychological distress [30]. However, the generalization of these results is limited because most participants were female patients with breast cancer. A large part of lung cancer patients already have advanced cancer at time of diagnosis and are confronted with a poor prognosis and low health status. Consequently, they more often report psychological distress than patients with other diagnoses of cancer [8,9]. Hence, it is not yet clear whether MBSR is a feasible, acceptable and effective intervention in patients with lung cancer. Moreover, little is known about the effectiveness of MBSR in partners of cancer patients [30], though they also often report psychological distress.

Our pilot study of 19 lung cancer patients and 16 partners participating in an MBSR course, provides preliminary evidence that MBSR is feasible and acceptable in this population ([name], [name], [name], [name] and [name], in preparation). The current trial will answer the question whether MBSR is effective in patients with lung cancer and their partners.

We started enrolment of participants in February 2012. At the moment, we think recruiting a sufficient number of patients and partners will be a challenge due to rapidly fluctuating health status and sudden changes in cancer treatment [77]. The main reasons for declining participation in patients is ‘being too ill’ or that it is ‘too much of a burden during chemo and/or radiotherapy’. Furthermore, no perceived need or motivation for the training is commonly mentioned. Among partners, participation is highly depending on whether the patient is willing to participate. Although partners can take part separately, partners who are interested do often not participate when the patients decline participation.

Considering the difficulty of studying lung cancer patients and their partners [77], our trial will offer valuable information on whether MBSR, as one of the few available psychosocial care programmes, contributes to the alleviation of their psychological distress.

## Abbreviations

MBSR: Mindfulness-based stress reduction; RCT: Randomized controlled trial; RUNMC: Radboud University Nijmegen Medical Centre; MBCT: Mindfulness-based cognitive therapy; MMSE: Mini mental state examination; DT: Distress thermometer; HADS: Hospital anxiety and depression scale; QLQ-C30: Quality of life – cancer; QLQ-LC13: Quality of life – lung cancer; SIP: Sickness impact profile; SPPIC: Self-perceived pressure from informal care; CRA-SE: Caregiver reaction assessment – care-derived self-esteem; IMS-S: Investment model scale-satisfaction; MIS: Mutuality and interpersonal sensitivity; SAIL: Spiritual attitude and involvement list; FFMQ: Five facet mindfulness questionnaire; SCS: Self-compassion scale; RRS-EXT: Rumination response scale – extended version; IES: Impact of event scale.
